The secondary objective is to assess the effectiveness of the extended maintenance intervention compared to the control group on self-reported BMI in children 7–14 years old 1 year after the completion of health camp (secondary outcome). We hypothesize that children receiving the extended maintenance intervention will be more likely to maintain a healthier BMI compared to the control group.

The following research questions form the basis of the evaluation:

Process evaluation:

What are the characteristics of the children and families maintaining their results after 3 months and 1 year despite not receiving the extended maintenance intervention?What are facilitators and barriers in implementation of the extended maintenance intervention in the family and from intervention coordinators?What was the actual dose of intervention in the standard vs. the extended maintenance intervention and the association to the primary and secondary outcomes?

Effect evaluation:

Can an extended maintenance intervention after participating in a residential health camp maintain results on the primary outcome life satisfaction measured on the Cantril ladder and secondary outcome BMI 1 year after the completion of health camp (primary and secondary outcome) or at short-term follow-up (3 months after health camp)?Can an extended maintenance intervention after the residential health camp maintain results on intermediate outcomes: self-efficacy, self-esteem, social relations, health promoting behavior (food, exercise, sleep), school satisfaction, body satisfaction, and parental health promoting behavior, and parental self-efficacy after 3 months and 1 year.

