#### Sampling and Allocation to Intervention Groups

Half of the children from the Liljeborg health camp is offered the extended maintenance intervention. The allocation to the intervention group is done by a secretary at the DCSH. The allocation is not random but based on the home municipality of the child (geographical criteria). The Liljeborg health camp covers both municipalities in the Capital Region of Denmark and the Region of Zealand and the distribution is ~50/50 from each region. All 10 municipalities in the Region of Zealand covered by the Liljeborg health camp are allocated to the intervention group. The control group includes children from the Liljeborg health camp along with the four other health camps receiving the standard maintenance intervention (control group 1) and children from the Liljeborg health camp allocated to the standard maintenance intervention (control group 2).

Blinding is not possible in this setting, and the standard maintenance intervention families at Liljeborg will have an idea of the activities going on in the extended maintenance intervention. For the four remaining health camps, families are not aware of any other type of maintenance interventions than the one offered at that specific home, which is the standard maintenance intervention.

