##### Child Questionnaires

The questionnaires were expanded by the research group and new items were added by the research group. The items were based on scientific literature, experience from child surveys in general and existing questionnaires from the DCSH. The majority of items were taken from the Health Behavior in School-aged Children (HBSC) study (33). In order to identify items which reflects areas the children find especially important when returning to their homes, we also performed two focus group interviews among a total of 12 children at the Liljeborg health camp who had been home for 4 weeks. The final questionnaire was pilot tested in 24 children. The pilot test showed that the youngest children or children with reading difficulties had difficulties in reading some of the items. Therefore, we decided to add audio reading to the questionnaires which enables a child to have the items read aloud if needed.

The first two questionnaires will be filled out at the health camp which means that the response rate is expected to be close to 100% for these two questionnaires for the children who complete a stay at health camp. A schoolteacher or a pedagogue at the camp will be encouraged to help especially younger children as well as older children if they are unsure about the meaning of an item. The short-term and long-term questionnaires are web-based questionnaires which are sent to the parents' email addresses.

The questionnaires at baseline and long-term follow up are identical. In the post health camp questionnaire items about context at home e.g., school environment and friends are taken out since the children have not been part of everyday life in their home environment for 10 weeks. The short-term follow up questionnaire is identical to baseline and long-term questionnaires but with a few items about how it has been to return home from health camp and if they feel they got enough support from their surroundings.

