**Explorative outcomes**					
Parent's report of child's life satisfaction	*Here is a picture of a ladder. Suppose the top of the ladder represents the best possible life for your child and the bottom of the ladder the worst possible life for your child. Where on the ladder do you feel he/she stands at the present time?*	Cantril ladder (modified to parents from HBSC)	Parents	– Baseline – Post health camp – Short-term follow up – Long-term follow up	0–10
Well-being	*Over the last two weeks: I have felt cheerful and in good spirits I have felt calm and relaxed I have felt active and vigorous I woke up feeling fresh and rested My daily life has been filled with things that interest me*	WHO-5(52)	All children	– Baseline – Post health camp – Short-term follow up – Long-term follow up	5 (all the time) to 0 (at no time)
	*In the last 6 months: how often have you had the following…? headache, abdominal pain, backache, feeling low, irritability or bad temper, feeling nervous, difficulties in getting to sleep or feeling dizzy*	HBSC Symptoms checklist	All children	– Baseline – Post health camp – Short-term follow up – Long-term follow up	4 (almost every day) to 0 (never)

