### Data Analysis

We will use descriptive statistics to investigate baseline equivalence and loss to follow up. We will graphically visualize the development over time in both intervention group and control group 1 for the primary and secondary outcomes.

We will analyze the effectiveness of the extended maintenance intervention compared to control group 1 on the primary and secondary outcomes, using linear regression analysis and on explorative outcomes using logistic regression analyses. We will apply an intention-to-treat approach including all children in the intervention group they initially have been allocated to irrespective of whether they have completed the intervention or are lost to follow-up. Missing data will be replaced by multiple imputation. We will perform complete case analysis for sensitivity analyses.

The effect analyses will be adjusted for baseline factors including gender and age of the child, life satisfaction, BMI-*Z* score, and parental socioeconomic position.

For the total population at all five camps, we will calculate the standard deviation of the primary and secondary outcomes right after camp to calculate Cohen's *d* effect size.

Furthermore, we will perform sensitivity analysis restricted to the data from the Liljeborg health camp to identify any differences between camps (control group 2). We will investigate the association between intervention dose and effect (per protocol analyzes).

We will investigate if the effect differs by subgroups (see moderators in Figure 2).

We will summarize process measures using appropriate descriptive statistics including proportions, means (SD), and medians (IQR).

We will identify who is in most need of the intervention and find out who does not need the intervention.

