## Discussion

This paper describes the study protocol for a quasi-experiment of an extended maintenance intervention, which aims to maintain positive benefits of an initial 10-week stay at a residential health camp on children's life satisfaction and BMI after they have returned to their homes. Both the initial intervention at the health camp, the standard maintenance intervention (control group) and the extended maintenance intervention are developed by practitioners and delivered for other purposes than research.

Center for Intervention Research, at The National Institute of Public Health, SDU in Denmark was commissioned by the Liljeborg Foundation and the DCSH to conduct an external research-based evaluation of the implementation and effectiveness of the intervention. It is however challenging to evaluate real world practice in a rigorous research design.

The practical set-up of the health camps and the maintenance interventions limited our methodological opportunities and forced us to make some compromises to the ideal research design. We would have preferred to conduct a RCT study, but it will not be possible to randomize children into intervention and control groups as the DSCH controls the allocation procedure. Instead we will approach the evaluation as a quasi-experiment with the risk of selection bias (30). We do not expect large systematic differences between the two groups as the DSCH's allocation procedure is motivated by which municipality the child comes from and both intervention and control groups recruit children from municipalities with a different socioeconomic range. However, we will assess baseline equivalence between the two samples using descriptive statistics on key variables and we will adjust the effect analyses for key covariates chosen a priori. The study is also limited by the self-reported height and weight measures at 3 months and 1 year follow up (45, 46). However, we hypothesize that a potential disagreement between objective measures and self-reported measures will be similar in both intervention and control groups. The objective and self-reported measures at baseline and post camp will enable us to explore this hypothesis.

The strengths of this study include the use of external evaluators, the systematic approach to evaluation planning, the research-based evaluation design, the prospective trial registration, and the development of a program theory to structure the evaluation.

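### The covariate list for the effect analyses does not name the outcome's own baseline for explorative and intermediate outcomes, although it is collected and allocation is not random

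*Protocol article*

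**What the plan says.** All references are to the protocol article.

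- **Covariates (Data Analysis).** "The effect analyses will be adjusted for baseline factors including gender and age of the child, life satisfaction" is followed by BMI-Z score and parental socioeconomic position. The subject of the sentence is the effect analyses in general, and no other covariate list appears. The Discussion describes the adjustment this way: "we will adjust the effect analyses for key covariates chosen a priori".
- **Models (Data Analysis).** The comparison is made "on the primary and secondary outcomes, using linear regression analysis and on explorative outcomes using logistic regression analyses". No model is named for intermediate outcomes.
- **Role of the other outcomes (Introduction, effect-evaluation questions).** The second question asks whether the extended intervention can "maintain results on intermediate outcomes: self-efficacy, self-esteem, social relations" and further measures, at 3 months and 1 year.
- **Baseline data.** Table 3 lists a baseline measurement for every explorative and intermediate outcome, from "Parent's report of child's life satisfaction" to parental self-efficacy. Of the child forms, the Child Questionnaires section says: "The questionnaires at baseline and long-term follow up are identical".
- **Allocation (Sampling and Allocation to Intervention Groups).** "The allocation is not random but based on the home municipality of the child". The Discussion accepts that this brings a risk of selection bias.

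**The concern.** Baseline life satisfaction and BMI-Z score are the own baselines of the primary and secondary outcomes, so those two models are well specified in this respect. For every other outcome, the named list supplies the baseline of a different variable. A model for WHO-5, diet, exercise or parental self-efficacy would contain baseline BMI-Z score but not, by name, the baseline of the measure being analysed.

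In a randomised trial this would mainly cost efficiency. Here the groups come from different municipalities and, for most controls, from different camps, so baseline differences are not ruled out by design. The plan's safeguards are a descriptive check of baseline equivalence and covariate adjustment. A description shows a gap but does not remove it, and the named adjustment omits the most direct control for it.

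The results at stake are those that answer the second effect question and bear on the steps of the program theory. They include body satisfaction, which the Ethical Issues section relies on to learn whether the focus on weight does harm. A pre-existing difference there could hide harm or imitate it.

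**Working it through.** **1. The plan's own figures.** Inputs from Sample Size Calculations: SD 2.1, power 80%, groups of 144 and 894, or 132 and 822 after 8% dropout. No alpha is stated; two-sided 0.05 is assumed.

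Detectable difference = (1.960 + 0.842) × SD × √(1/n₁ + 1/n₂)

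- 144 and 894: 2.802 × 2.1 × 0.0898 = 0.528 (plan: 0.53)
- 132 and 822: 2.802 × 2.1 × 0.0938 = 0.552 (plan: 0.55)

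Both reproduce. One-sided 0.05 gives 0.47 and 0.49 and does not. No stated figure is in dispute.

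**2. Linear scale.** The documents give no correlations, so these are assumed:

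- r, own baseline with follow-up: 0.3 to 0.7
- a, own baseline with baseline life satisfaction: 0 to 0.5
- gap D between groups in the own baseline: 0.2 SD
- life satisfaction related to follow-up only through the own baseline; other covariates ignored

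Bias without the own baseline = r × (D − a × d), where d is the group difference in baseline life satisfaction.

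SE without ÷ SE with the own baseline = √[(1 − a²r²) / (1 − r²)].

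| r | Bias, d = 0 | Bias, d = 0.2 SD (a from 0.5 to 0) | SE ratio (a from 0.5 to 0) |
|---|---|---|---|
| 0.3 | 0.06 SD | 0.03 to 0.06 SD | 1.04 to 1.05 |
| 0.5 | 0.10 SD | 0.05 to 0.10 SD | 1.12 to 1.16 |
| 0.7 | 0.14 SD | 0.07 to 0.14 SD | 1.31 to 1.40 |

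Lowest case: 0.3 × (0.2 − 0.5 × 0.2) = 0.03. Highest: 0.7 × 0.2 = 0.14. When life satisfaction differs in the same direction and is correlated with the outcome's baseline, adjusting for it removes part of the gap.

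**3. Logistic scale, the model stated for explorative outcomes.** Simulation with 144 and 894 children, r = 0.5, a = 0.3, life satisfaction balanced, outcome split at zero on the latent scale, 1,500 runs per scenario. Both models contain life satisfaction.

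| Scenario | Quantity | Without own baseline | With own baseline |
|---|---|---|---|
| No gap, no effect | Rejection rate | 4.2% | 4.9% |
| Gap 0.2 SD, no effect | Mean log odds ratio | 0.16 | 0.00 |
| | Rejection rate | 13.5% | 5.5% |
| No gap, effect 0.25 SD | Mean log odds ratio | 0.402 | 0.472 |
| | SE | 0.185 | 0.200 |
| | Power | 59% | 68% |

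Monte Carlo error is about 0.9 points on the 13.5% (√(0.135 × 0.865 / 1500)) and about 1.3 points on the power figures. In the last scenario the SE is smaller without the own baseline, but the coefficient shrinks more: 0.402 / 0.185 = 2.17, against 0.472 / 0.200 = 2.36. That is where the power goes.

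**The case against.** The case against has real weight.

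- **The list is open.** A reader might infer that the plan fixes a closed set and excludes own baselines. The sentence does not say that: it introduces the factors with *including*, and nothing states that an own baseline will be left out. The omission is read from the only list given.
- **This is a condensed article.** Covariates for lesser outcomes are often left to a full protocol or SAP, which is not shown. Silence alone would be no finding. But the article does state an adjustment set for the effect analyses and says the covariates were chosen in advance. Followed as written, that set gives the weaker analysis. An open list also leaves room to choose covariates outcome by outcome after the data are seen, which sits badly with that commitment.
- **The main outcomes are handled.** This stands in full.
- **Not all of a baseline gap would carry over.** A reader might infer that the whole difference passes into the result. It does not: the part shared with life satisfaction, BMI-Z score, age, gender and socioeconomic position is removed.
- **Intervals would not necessarily be wider.** A reader might infer a loss of precision in that form. It holds for a linear model, but the article assigns logistic regression to explorative outcomes. The Ethical Issues section treats body satisfaction, intermediate in Table 3, as explorative, so logistic models may reach further. There the loss shows as an odds ratio closer to one and lower power.
- **The added covariate is not always clean.** Some items carry non-ordinal codes, such as a don't-know option or not having the person asked about, and several go only to children aged 10–14. This stands and shapes the fix.

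**Conclusion.** The point holds in a limited form. The named covariates cover the own baseline of the primary and secondary outcomes and of no other outcome, although all are scheduled at baseline and the groups are not randomised. If the list were followed as written, the unexplained part of a baseline difference would enter the explorative and intermediate estimates, and some power would be lost.

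The sizes are illustrations. The 0.03 to 0.14 SD of bias needs a 0.2 SD gap and the assumed correlations. The 13.5% against about 5%, and the 59% against 68%, come from one logistic set-up. The documents neither show that such a gap exists nor give any of these correlations. No primary or secondary conclusion is affected, so this is a minor improvement.

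**What to change.** Add a sentence to Data Analysis along these lines:

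> For each explorative and intermediate outcome, the effect analysis at 3 months and at 1 year also adjusts for the baseline value of that outcome, where the item was asked at baseline. Response codes without an order are entered as categories or set to missing. The same baseline values enter the imputation model.

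The cost is small: one extra parameter per model, or a few where the baseline item is categorical. The data are already scheduled, with no added participants or procedures. The one gap is children not asked the 10–14-year items before camp, who have no baseline value; the plan should say how they are treated. The primary and secondary models stay as they are.

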#### Intervention Group: Extended Maintenance Intervention

The extended maintenance intervention is also delivered by an intervention coordinator who is assigned to a family. Some activities are identical to the standard maintenance intervention such as family day and follow up day along with phone calls (Table 1). The extended maintenance intervention encompasses several new initiatives compared to the standard maintenance intervention. It has a duration of ~16 weeks, 6 weeks while the child is at camp and 10 weeks afterwards. The intervention coordinator will participate in home visits and can also participate in different activities such as school visits and network meetings and assist the family in initiating new sports activities or other relevant activities (Table 2). The number of each of the activities are decided in corporation between the family and the intervention coordinator. The intervention has been in constant development since the beginning of 2018 and it is an ongoing process.

**Table 1 T1:** Main similarities and differences between the two maintenance interventions.

**Family collaboration**	**Standard maintenance intervention (control group)**	**Extended maintenance intervention (intervention group)**
Intervention provider	Intervention coordinator	Intervention coordinator
Duration	9 weeks	16 weeks
Intervention concept	Standard	Tailored to each child
Information day before camp	X	X
Family day during camp	X	X
Follow up day 4 weeks after camp	X	X
Phone call/texts to follow up	X	X
Home visits during and after health camp		X
Network meetings		X
School meetings		X
Meeting with health worker or social worker in home municipality		X
Start-up of sports activities		X

**Table 2 T2:** Activities in the extended maintenance intervention and frequency.

**Activities**	**Number**
**Home visits:** The intervention coordinator visits the child's home and talks to the parents and the child, most often separately. The first visit is while the child is still at camp and therefore solely involves a talk with the parents	2–5
**Network meetings:** The intervention coordinator arranges a meeting with relevant participants e.g., parents, schoolteacher, school principal, social and/or health worker from the municipality etc.	0–2
**School meeting:** The intervention coordinator visits the schools along with the child to tell the classmates about the child's experiences at the camp	0–1

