**Meetings with health worker or social worker in home municipality**: The intervention coordinator can have contact to relevant people in the home municipality to insure relevant support to the family.	0–3
**Conversations with child:** If the intervention coordinator finds it necessary; she can have talks with the child alone. It is most common in the teenage children.	0–3
**Support to start up new sports activities:** The intervention coordinator supports the child in considering and identifying local sports offers and clubs to join. Sometimes the coordinator is presents at the child's first practice.	0–1
**Follow up by phone, e-mail, text messages:** The parents or child have contact with their intervention coordinator in between visits and activities as needed by the family.	0–??

The intervention coordinators' extended maintenance intervention in each family is guided by the so-called Life Satisfaction Compass, which is developed by the staff at the Liljeborg health camp and based on Prochaska and DiClemente's Stages of Change model (31). In collaboration with the staff at the Liljeborg health camp and the family's own intentions, the intervention coordinator uses the compass as a screening tool to identify the needs of each child and family to customize the intervention to them. It has eight focus areas: workout habits, dietary habits, network, family culture and structure, coping strategies, leisure life and communities, school life, and the child's general life satisfaction. Thus, the intervention may be tailored to address all or only a few areas of the compass important for the specific child and family. It is a dynamic intervention where the intervention coordinator continuously evaluates what needs to be the focus for the specific child or family. The intervention is designed to be easy and meaningful for the families to participate in since the intervention coordinators visit them at home and customize the intervention to each family making. Also, it is considered okay if the families do not feel like they need the help and therefore end the extended maintenance intervention, although it seems like very few families do this.

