#### Data for Process Evaluation

Process evaluation is recommended by the Medical Research Council in complex intervention (35). If the effect evaluation is done in isolation, it may leave essential questions unanswered and in the case of ineffectiveness we will not be able to differentiate between implementation or theory failure (35). Thus, the overall aim of the process evaluation study is to measure implementation of the extended maintenance intervention to enable analyses of how implementation fidelity affects the effect of the primary and secondary outcomes (per protocol analyses).

To detect levels of fidelity we will measure if the intervention coordinators implement the intervention to their initial goals as part of the action plan in order to identify possible implementation failures or to identify if the intervention and its assumptions for the working mechanisms suffer from theory failure.

In the case of effect, we want to be able to characterize if certain aspects of the intervention seem more likely to result in an effect and if e.g., if certain combinations of activities seem more effective.

Furthermore, we will identify facilitators and barriers for the implementation of the extended maintenance intervention to guide refinement of the intervention before it is up scaled to other DCSH health camps.

The process evaluation study will be structured according to the program theory and key process evaluations measured inspired by the Medical Research Council guidelines (35), a systematic process evaluation protocol (36), and the conceptual framework presented by Steckler AND Linnan (37). The process evaluation will combine multiple quantitative and qualitative data collection methods including questionnaires, workshops, participant observations, and interviews.

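### The dose–outcome association is labelled per protocol, but dose follows need and family choice, so it is confounded and a low dose can be full adherence

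*Protocol article*

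**What the plan says.** Three places in the protocol article plan the analysis.

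- Data Analysis: "We will investigate the association between intervention dose and effect (per protocol analyzes".
- Introduction, under the process-evaluation research questions: "What was the actual dose of intervention in the standard vs. the extended maintenance intervention and the association to the primary and secondary outcomes".
- Data for Process Evaluation, where the aim of measuring implementation is "enable analyses of how implementation fidelity affects the effect of the primary and secondary outcomes (per protocol analyses". That section wants to tell implementation failure from theory failure, to see whether certain activities or combinations seem more effective, and to guide refinement before the programme is extended to other camps.

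The section on the extended maintenance intervention says how dose arises.

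- The coordinator "uses the compass as a screening tool to identify the needs of each child and family to customize the intervention to them".
- "The number of each of the activities are decided in corporation between the family and the intervention coordinator". Table 2 gives ranges, such as 2–5 home visits and 0–3 municipality meetings.
- "It is a dynamic intervention where the intervention coordinator continuously evaluates what needs to be the focus for the specific child or family".
- On stopping early, "it is considered okay if the families do not feel like they need the help and therefore end the extended maintenance intervention", with the remark that very few families seem to do so.

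The Perspectives section adds that content, dosage and length rest on the provider's judgement. In the standard arm, extra phone calls are made where needed.

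The only adjustment listed for the effect analyses is for baseline gender, age, life satisfaction, BMI-Z and parental socioeconomic position. Baseline is measured before camp.

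**The concern.** A per-protocol analysis needs a protocol treatment to adhere to. Here the number of activities is an output of the tailoring. Two home visits may be complete delivery for one family and under-delivery for another, yet a dose regression scores both as low implementation.

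The same label also covers two different quantities. Data for Process Evaluation defines fidelity as whether coordinators implement to the initial goals in the action plan, which is delivered against planned. Data Analysis attaches the label to the amount of intervention.

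Whatever drives dose may also drive the 1-year outcome. Children with more difficulties may get more support and do worse. Engaged families may take up more and do better. Either would produce an association without any effect of dose. The result is meant to separate implementation failure from theory failure and to show which activities work, so a spurious slope in either direction could misdirect how the programme is refined before it is extended.

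**Working it through.** **The plan's own figure, as a yardstick.** The plan gives no figure for the dose analysis. Its detectable group difference can be reproduced with SD 2.1, 80% power and two-sided 5% (the significance level is not stated; this one matches):

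(1.960 + 0.842) × 2.1 × √(1/144 + 1/894) = 0.528, stated as 0.53.

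With 132 and 822 children the result is 0.552, stated as 0.55. These figures are sound and serve below only for scale.

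**Timing of need and adjustment.** Baseline precedes the 10-week stay. The extended intervention lasts about 16 weeks, 6 at camp and 10 afterwards, so it starts about 4 weeks into camp, and its focus is re-evaluated throughout. Need that emerges at camp or at home can alter dose but is not in the listed covariates.

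**What a zero dose effect would look like.** Taken from the documents: outcome SD 2.1, and n = 132 in the intervention group. Assumed, because the documents give no values:

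- baseline–outcome correlation 0.5;
- dose–baseline correlation -0.3 (lower life satisfaction, more support);
- need N not captured by baseline, with correlation r_N with dose and g_N with outcome;
- family engagement M, with correlation r_M with dose and g_M with outcome;
- B, N and M mutually independent, where B is baseline life satisfaction, standing in for the planned covariates.

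The expected slope per SD of dose, with true effect zero, is

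- unadjusted: 2.1 × (-0.3 × 0.5 + r_N g_N + r_M g_M);
- adjusted for baseline: 2.1 × (r_N g_N + r_M g_M) / (1 - 0.3²), with denominator 0.91.

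The last two columns come from simulation, with 4,000 runs per row and a two-sided 5% test. Simulated mean slopes agree with the formula to within 0.005.

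| Scenario (adjusted for baseline) | Formula | Simulated slope | Significantly negative | Significantly positive |
|---|---|---|---|---|
| Need fully captured by baseline | 0 | -0.001 | 2.4% | 2.7% |
| r_N 0.3, g_N -0.3 | 2.1 × (-0.09)/0.91 = -0.21 | -0.211 | 24% | <0.1% |
| r_N 0.5, g_N -0.3 | 2.1 × (-0.15)/0.91 = -0.35 | -0.348 | 56% | 0% |
| r_N 0.5, g_N -0.5 | 2.1 × (-0.25)/0.91 = -0.58 | -0.574 | 95% | 0% |
| r_N 0.5, g_N -0.3; r_M 0.5, g_M 0.3 | 2.1 × 0/0.91 = 0 | 0.005 | 2.0% | 2.9% |
| r_N 0.3, g_N -0.3; r_M 0.5, g_M 0.3 | 2.1 × 0.06/0.91 = +0.14 | 0.137 | 0.2% | 12% |
| r_N 0.2, g_N -0.3; r_M 0.5, g_M 0.3 | 2.1 × 0.09/0.91 = +0.21 | 0.211 | <0.1% | 24% |
| r_N 0, g_N -0.3; r_M 0.5, g_M 0.3 | 2.1 × 0.15/0.91 = +0.35 | 0.343 | 0% | 55% |

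In the first row the unadjusted slope is 2.1 × (-0.15) = -0.315 (simulated -0.32, significantly negative in 42% of runs). The planned adjustment removes all of it. What remains in the other rows comes from need and engagement that baseline does not show.

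**The case against.** Much can be said for the plan.

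- Data Analysis and the research question both speak of association, and the question sits under process evaluation. This stands, but Data for Process Evaluation gives the analysis under the same label a causal purpose, and nothing in the article warns that need confounds dose.
- Baseline life satisfaction and BMI-Z are already planned covariates, and where they capture need the bias disappears. This stands and is the first row of the table. It does not cover need that arises after baseline.
- Fidelity as delivered against planned is already foreseen. Coordinators record planned focus areas, focus areas during the intervention and what was finally delivered, using measures inspired by goal attainment scaling. This stands, and it is why the fix is cheap. The per-protocol label in Data Analysis is nevertheless attached to dose.
- Covariates and dose definitions for a secondary analysis may be in a full plan that is not shown. This is fair. The point rests on the label and the purpose that the article states.

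A reader might infer that the analysis is bound to show worse outcomes with more support. The documents do not support that. Families share in setting dose, so engagement can cancel or reverse the slope, and the Perspectives section itself expects implementation to go with better effects. Nor can early stopping by families who feel well be taken as the main driver, since the article says very few families stop. Tailoring is the stronger mechanism.

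**Conclusion.** The concern holds as one of labelling and confounding. No protocol dose exists, a low dose can be full adherence, and the dose–outcome association mixes any effect of dose with need and engagement. It can be spurious in either direction: about -0.57 to +0.34 points per SD of dose in the scenarios above, and zero if baseline captures all need and engagement plays no part. At the extremes this is of the same order as the 0.53-point group difference the study is sized for, although a slope per SD of dose and a group difference are not the same quantity. The range depends wholly on the assumed correlations, and the documents determine neither sign nor size.

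A reader might also infer that the main result is compromised. It is not: the intention-to-treat comparison does not use dose.

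**What to change.** In Data Analysis, reserve the per-protocol label for delivered versus planned focus areas, in line with the action-plan goals in Data for Process Evaluation and the data described under Intervention Coordinator Questionnaires.

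For regressions of outcome on dose:

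- drop the per-protocol label;
- adjust for the Compass focus areas recorded before the intervention, and for end-of-camp life satisfaction and BMI-Z, in addition to the listed baseline covariates;
- report the results as exploratory and non-causal.

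All these data are already planned. The Compass questionnaires cover only the extended arm, so a dose model in the standard arm would rely on the baseline and end-of-camp measures. Need that first appears after the return home stays unadjusted, which is why the non-causal label is needed as well.

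A complier-average analysis is not a substitute as the main remedy. Allocation is by municipality and not random, and such an analysis yields a single effect of receipt, which does not answer the dose question.

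The cost is a change of wording, slightly wider intervals, and a small risk of over-adjustment, because the extended intervention begins during camp and may already influence end-of-camp values. Showing the dose models with and without the end-of-camp covariates would make that visible.
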